**Introduction:**

In an earlier study done in Uganda by Kakooza Mwesige et al, a high rate of premature mortality among children with CP at the Iganga Mayuge health and demographic surveillance sites, was suspected following the noticeable decrease of CP prevalence with age. High rates of malnutrition, frequent comorbidity and severe impairment were alleged to be contributory. The high prevalence of malnutrition in the CP child population in Uganda is further reiterated by Kakooza Mwesige et al among a clinical CP child cohort at the Mulago regional referral hospital, as 52% especially among those who are five years or older [^1^](#_ENREF_1) . Malnutrition is a multifaceted condition which if not managed effectively may affect the overall health outcome of a child with CP, including their comorbidity status and impairments progression. However, efforts to curb malnutrition although evident among the typical child population, are less proven among children with disabilities including CP [^2^](#_ENREF_2) [^3^](#_ENREF_3)^,^ [^4^](#_ENREF_4) [^5^](#_ENREF_5). Children with CP spend most of their time with caregivers, hence management of CP child malnutrition should actively involve primary child caregivers.

The Positive deviance (PD) approach is one of the caregiver led strategies that has revealed nutritional success in the typical child population in some African settings [^6^](#_ENREF_6)^,^ [^7^](#_ENREF_7). The PD approach operates on the premise that in most population distributions, for example in the field of nutrition, there is a statistically defined portion of the highly malnourished population who deviate positively from the population mean (outliers), and fall within the range of the normally nourished (positive deviants)[^8^](#_ENREF_8). This study thus seeks to evaluate the effectiveness of positive deviance and parent facilitator training strategies to malnutrition in the CP child and youth population, so as to enhance health promotion and survival in this vulnerable population.

This study will be hinged on the cerebral palsy in Uganda risk factors, intervention and epidemiology (CURIE) research project which has implemented at the Iganga Mayuge health and demographic surveillance sites (IM-HDSS) in eastern Uganda since 2015. The CURIE project conducted the CP prevalence study in 2015 identifying 97 children with CP through a three stage screening process[^9^](#_ENREF_9). Ninety seven age and sex matched controls without CP were also recruited in 2015 for the CURIE follow-up study utilizing the CURIE prevalence study findings as baseline, and later conducting follow-up assessments in 2019. Using similar tools, gross and fine motor function, and nutrition and clinical examination assessments were made at the two points of assessment in 2015 and 2019 among the same study population of children with CP and their matched controls. An intervention study (Akwenda) was there after conducted by the CURIE study team between 2021 and 2022 in which effectiveness of a comprehensive intervention among surviving children with CP was tested. The Akwenda intervention included a Carer-to-Carer approach (parent facilitator trainings) on child functional outcomes, and caregiver quality of life, and a communication and advocacy intervention to improve community perceptions towards CP. The current study will utilize the CURIE intervention study arms to answer its intended objectives while using the same study population.

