**Sample size estimation:**

1. **Sample size estimation in a between subjects 2x2 factorial design (Bonnet,2016)**

**
[figure not shown]
**

In order to estimate a main effect in a between-subjects 2x2 factorial design at 95% confidence, at desired confidence interval width of 2.0, and a planning value of 8.0 for the average within group error variance, the contrast coefficients are 0.5, 0.5,-0.5 and-0.5, and the sample size required per group is approximately 31.

1. **Sample size estimation using two proportions:**

The PD program has been reported to increase weight of ≥200g in 12 days among 87% of participants in Burundi [^10^](#_ENREF_10). Based on the prevalence of malnutrition (<-2sd in any of HAZ,WAZ,BMIZ) among the CURIE CP population based cohort reported as 64% as per the 2015 assessments. Assuming the previously reported effect of the PD program, we hope to reduce malnutrition in the CP child population to about 29%, at α =0.05, and power (1-β) =0.8. After imputing these parameters into a Stata program to estimate sample size for individual randomization, of a two proportions test, the estimated total sample size is 62: Hence 31 participants per each of the four arms. Therefore for a 2x2 factorial trial, assuming a 1:1:1:1 allocation, 124 participants will be required for the study with 32 participants in each of the four conditions.

Participants in this study will include eligible caregivers of children with CP participating in the wider CURIE intervention study (Akwenda). In order to account for those that may not be malnourished from the CURIE study sample, additional caregivers of malnourished children with CP will be recruited from community-based organizations (CBOs) operating within the study setting including EKISA ministries and MUSANA community health centre. The CURIE intervention study has got two arms (PFT and Control) separated as village clusters based on geographical proximity and balanced by age, and GMFCS level. This study will utilize the available CURIE intervention clusters to avoid contamination. Details of participant recruitment from different CBOs are displayed below.

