**Positive deviance nutrition rehabilitation intervention:**

The PD-program will run for 3-months with 2 weeks sessions (12 days) conducted in each month. Each day sessions will include a half hour education session and a one and half hour peer led cooking session. Education sessions will be introduced through situational discussions and illustrated by an educational medium such as an appropriate game or a message. Caretakers will learn how to rehabilitate their malnourished children under the supervision and the support of positive deviant caregivers. Children will be nutritionally assessed by trained nutrition assistants or clinician on the 1^st^, 6^th^, and 12^th^ day of the sessions and after three months.

Caregivers will learn how to prepare nutrient-rich meals for their children from locally available food identified during the PD-inquiry, and good feeding and hygiene practices. Caregivers will together prepare their own food menus based on the PD-inquiry good foods or what they can conveniently access but of equal nutritional value. The menus will include foods which are locally available and affordable and of balanced nutrient value. Food menus will be repeated at least twice within each monthly sessions. However, because the participating children in the PD program are malnourished, total calorie and protein intake in the menus will exceed the daily normal requirement. For sustainability, participating caregivers will contribute the foods and required ingredients during the sessions from those locally available. Caregivers will also learn how to be able to identify child malnutrition through clinical signs, and other common preventable illnesses in childhood. Names and anthropometric data from the sessions will be recorded so as to track changes in nutritional status[^6^](#_ENREF_6)^,^ [^7^](#_ENREF_7).

1. **Parent facilitator trainings.**

The Parent facilitator training (PFT) intervention is part of the wider CURIE community-based intervention study among children with CP at the IM-HDSS. The CURIE intervention study consists of an intervention and control group (1:1 ratio) selected from a previous cohort of surviving children with CP recruited in the CURIE follow-up study and other eligible children with CP selected from the Iganga Mayuge districts CBOs to make-up the desired sample size of 90 children with 45 children per arm. Ethical approval of the CURIE intervention study has been obtained at reference (SS 5173)

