The parent facilitator training programme is based on the Malamulele Onward Carer-2-Carer program (https://www.malamuleleonward.org/online-resources/c2c-materials) in South Africa. The program is designed to be delivered by parents/caregivers of children with CP in seven workshops that aim to improve CP child’s participation and activities of daily living (e.g, eating, dressing, and play).

**Training parent facilitators**: Four primary caregivers of children with CP from Iganga are trained as parent facilitators by physical therapist. The training involves four weeks of training from a master trainer from Malamulele Onward, herself a parent of a child with CP. Each workshop is approximately two hours long and includes between 6-10 caregivers. Each workshop is led by two parent facilitators who work as a team. To ensure quality and consistency of the workshops, the Parent Facilitators follow a detailed manual adapted from the Malamulele Onward Carer-2-Carer Programme translated into *Lusoga*, the local language. For each workshop the Parent Facilitators have a workshop kit, which includes display materials. No therapist will be involved in the monthly parent-led workshops. Two weeks after the workshops, caregivers and their children will attend a therapist-led practical group session which will have the same theme as the parent-led workshop.

**Parent facilitator-led sessions:** Parent facilitator sessions are held at a convenient community center. At the start of parent facilitator led sessions, caregivers are given a pretest on their knowledge about CP and caring for a child with CP including basic nutrition knowledge. A similar post –test assessment will be done at the end of the training program. Parent facilitator trainings involve 7 sessions that expose caregivers to understanding CP and how to improve body functioning: session1: what is CP? session2: CP as a way of life, Session 3: Getting my child’s body ready to move, Session 4: Eating and drinking a healthy diet, Session 5: communication, Session 6: Play, and Session 7: Central visual impairment. The therapists conduct regular monitoring and evaluation site visits to rural communities where the parent facilitators are working for ongoing training and up-skilling[^19^](#_ENREF_19).

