**Randomization and blinding:**

**Randomization of participants from the CURIE (Akwenda) intervention study**: Eligible children with CP in the intervention group of the CURIE intervention study will be randomly assigned to receive PFT conditions so as to create the “both PD and PFT”, and “only PFT” conditions, as these individuals will receive PFT by default of the CURIE study. Likewise, participants in the CURIE control group will be randomly assigned to receiving, the “only PD condition”, and the “control” (neither PD nor PFT) condition.

**Randomization of participants from other organisations:** Since not all the CURIE intervention study participants may be eligible to participate (malnourished), other eligible caregivers and their children with CP sampled from elsewhere in the study site will be allocated to either the PFT or control groups of the CURIE study arms based on home village vicinity to make up the required sample for each of the four experimental conditions. Research assistants will be provided with the allocation of all participants after the baseline survey.

In order to avoid contamination, participants in the CURIE-intervention study have been allocated to clusters depending on the village where they reside. Neighboring villages were clustered together to reduce contamination between groups resulting in two geographically defined groups matched for age, sex and motor function. Given the similarity in study sites of the CURIE- study and this study, participants in our study will be allocated based on the already determined CURIE-intervention or control group village clusters as earlier described to avoid contamination. Participants in the control condition will be on waiting list to receive the PFT intervention later owing to the design of the wider CURIE study arrangement.

**Blinding:** Evaluators will be blinded on group allocations so that parent facilitators and caregivers do not report their subjective outcome measures differently. A group of independent outcome assessors (evaluators), not involved in the intervention, will administer the outcome measures after the interventions. These examiners will be blinded to group allocation to avoid reporting bias.

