**Study Implementation plan:**

This study and preceding qualitative assessments will be implemented as follows: In the first month, a situation analysis (nutrition survey) will be conducted by trained data collectors or clinicians to identify well-nourished and malnourished children and adolescents with CP from selected organizations in the study area. In order to identify the unique practices of caregivers of well-nourished CP children identified from the nutrition survey, that set them apart from others within the same community, a qualitative survey will be conducted during the second month. From this qualitative survey, a Positive Deviance Inquiry (PDI) report that documents the identified successful practices and good foods will be generated. Based on the PDI report, a positive deviance (PD) program will be designed and evaluated against the Akwenda/CURIE caregiver training program (parent facilitator trainings -PFT) among malnourished CP children through a randomized clinical trial. The trial will be implemented for 3 months. Monthly Nutrition Education and Rehabilitation Sessions (NERS) for identified malnourished children and their caretakers under the PD program, and training sessions under the PFT program will be conducted concurrently. Monthly growth monitoring of all children in the study group will be done by an external team of assessors. In order to evaluate the main effect of the PD program and the PFT programs separately and in conjunction, data management, analysis and reporting will be done in the subsequent months.

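### The second factor is CURIE/Akwenda arm membership, described as a package broader than parent facilitator training, so its main effect and interaction are not shown to be attributable to that training alone

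*Protocol*

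**What the plan says.** The Study design section defines a 2x2 factorial trial with the factors PD (Yes/No) and PFT (Yes/No). The Data management and analysis section plans a two-way ANOVA for the independent main effects and their interaction. The Study Implementation plan gives the aim: "In order to evaluate the main effect of the PD program and the PFT programs separately and in conjunction".

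The second factor comes from an existing study:

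- Introduction: "The current study will utilize the CURIE intervention study arms to answer its intended objectives while using the same study population".
- Randomization and blinding: CURIE intervention-arm participants form the two PFT-Yes cells, "as these individuals will receive PFT by default of the CURIE study".
- Sample size estimation: "The CURIE intervention study has got two arms (PFT and Control) separated as village clusters based on geographical proximity".

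The content of that study's intervention is described more broadly. The Introduction says that in Akwenda the "effectiveness of a comprehensive intervention among surviving children with CP was tested", and lists the carer-to-carer approach "and a communication and advocacy intervention to improve community perceptions towards CP". The Interventions text says that the PFT "intervention is part of the wider CURIE community-based intervention study".

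**The concern.** The same arm is described in two ways. In the Introduction it received an intervention with at least two components. In the Study design, Sample size estimation, analysis and implementation sections, and in Table 1, it is the single component PFT. Nothing in the Protocol separates the other component from the PFT contrast.

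What the trial may conclude is at stake. Following the plan as written would credit parent facilitator training with any difference between the two CURIE arms, although the Protocol itself describes the intervention behind those arms as broader. The adjustment mentioned under Study strengths and limitations concerns differences in baseline factors. A component delivered alongside PFT is part of the exposure, not a baseline covariate, so that adjustment does not reach it.

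**Working it through.** **1. Which contrasts are affected.** Let δ be the effect of PFT, c the effect of the advocacy component, and a₁ and a₀ the shares of PFT-Yes and PFT-No families that it reached. With additive effects:

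- The PFT main effect estimates δ + c(a₁ − a₀). It equals δ only if c = 0 or a₁ = a₀. The Protocol gives neither a₁ nor a₀.
- Both conditions versus PD only, and PFT only versus control, carry the same extra term.
- The PD main effect averages two within-arm differences, so the term cancels. For CURIE participants PD is randomised within arm.
- In the interaction an additive c also cancels numerically. What is estimated is still how the PD effect differs between the two CURIE arms. Reading this as PD by PFT requires that advocacy does not itself change the PD effect, and the Protocol does not address that.

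**2. The plan's own precision figure.** Inputs from Sample size estimation: error variance 8.0, 95% interval width 2.0, contrast coefficients ±0.5. The formula is not visible in the text; the usual form for a contrast is

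n = 4 × variance × Σc² × (z/width)², with Σc² here the sum of squared coefficients = 4 × 0.25 = 1

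n = 4 × 8 × 1 × (1.96/2)² = 30.7, rounded up to 31 per group.

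This reproduces the stated 31, and 4 × 31 = 124.

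**3. Illustration of size.** The standard error of the main-effect contrast at 31 per cell is √(8 × 1/31) = 0.508. Suppose that PFT has no effect (δ = 0) and that advocacy reached only the PFT-Yes arm (a₁ − a₀ = 1). The chance of p < 0.05 is

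Φ(c/0.508 − 1.96) + Φ(−c/0.508 − 1.96)

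| Assumed c (units of the planning variance) | Chance of a significant PFT effect |
| --- | --- |
| 0 | 5% |
| 0.25 | 8% |
| 0.5 | 17% |
| 1.0 | 50% |

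The values of c are assumptions; the documents give none. The Protocol also does not name the measurement unit behind the variance of 8.0, so the table shows sensitivity and is not a forecast. The shift in the estimate is c whatever the sample size. If a₁ = a₀, the first row applies throughout.

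**4. What the text says about a₁, a₀ and timing.** The Introduction states the purpose of the advocacy component (community perceptions) but not where it was delivered. It reports Akwenda in the past tense, between 2021 and 2022. The Study Implementation plan runs PFT sessions alongside the PD sessions over 3 months and mentions no advocacy activity. Whether the arms differ in exposure to advocacy, before or during the trial, therefore cannot be determined.

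**The case against.** The strongest reply is that the Protocol does define PFT. The Interventions text describes one manual-based programme, Sample size estimation labels the arms PFT and Control, and the waiting-list controls are promised PFT and nothing else. Advocacy aimed at community perceptions may well have been area-wide, or finished before this trial, in which case it does not bias the contrast. This stands as a possibility, and it rules out saying that the PFT effect is biased. It does not settle the matter, because the Protocol never says where or when advocacy was delivered.

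Three stronger readings are tempting and are not supported:

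- A reader might infer that PFT-Yes is the whole Akwenda package and that PFT-No families receive none of it. No section says that advocacy was confined to the intervention villages.
- A reader might count the therapist sessions as a hidden co-intervention. The description of the programme says: "Two weeks after the workshops, caregivers and their children will attend a therapist-led practical group session". The therapists' site visits are described there too. Both are declared parts of PFT, so they are not confounders.
- A reader might infer that children recruited from other organisations receive different content within PFT-Yes. The Protocol describes only one PFT programme and allocates these children to the existing groups; a different version for them would be an argument from silence.

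The non-random, village-based allocation of the PFT factor is a separate issue, which the limitations section acknowledges.

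**Conclusion.** The point holds as a limit on attribution. PFT-Yes is membership of the CURIE/Akwenda intervention arm, and the Protocol describes that intervention as including a component other than PFT. The planned main effect and interaction are therefore not shown to be attributable to PFT alone. To say that they cannot be attributed to it would go too far.

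The size is unknown. It runs from zero, if advocacy reached both arms equally or had no effect on the outcome, to a shift equal to the full advocacy effect if only the intervention arm received it. The 17% and 50% figures rest on assumed effects of 0.5 and 1.0 units, the planning variance of 8, 31 per cell, no true PFT effect, and advocacy confined to PFT-Yes. The PD main effect among CURIE participants is not undermined by this point.

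**What to change.** In Study design, Data management and analysis, Study Implementation plan and Table 1, define the second factor as CURIE/Akwenda intervention arm versus control. State that its main component is PFT as described under Interventions, including the therapist-led sessions. Restrict the main-effect and interaction conclusions to that arm contrast, unless the Protocol documents that the communication and advocacy component reached both arms equally.

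The cost is a few sentences, with no change to sample size, allocation or data collection. The downside is a less specific claim about PFT.

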**Methods:**

**Study setting:** The study will be conducted within the districts of Iganga, Mayuge and Bugweri in eastern Uganda.

**Study design:**

This will be a 2x2 factorial quasi-randomized controlled trial assessing the effects of the Positive deviance (PD) (Yes/No) and Parent facilitator training (PFT) (Yes/No) strategies within four experimental conditions: i) Both PD and PFT, ii) Only PD, iii) Only PFT, iv) Neither PD and nor PFT (controls).

**Study population:**

The study population will include caregivers of malnourished children and youth aged 2-24 years old with a confirmed diagnosis of CP originally participating in the Akwenda intervention study. Additional new children with a confirmed CP diagnosis will be recruited from the study area to meet the sample size requirements.

Exclusion criteria: Caregivers registered in other nutrition interventions and those with severely malnourished children that require life-saving nutrition management will be excluded from participating in the study.

**Sample size estimation:**

1. **Sample size estimation in a between subjects 2x2 factorial design (Bonnet,2016)**

**
[figure not shown]
**

In order to estimate a main effect in a between-subjects 2x2 factorial design at 95% confidence, at desired confidence interval width of 2.0, and a planning value of 8.0 for the average within group error variance, the contrast coefficients are 0.5, 0.5,-0.5 and-0.5, and the sample size required per group is approximately 31.

1. **Sample size estimation using two proportions:**

The PD program has been reported to increase weight of ≥200g in 12 days among 87% of participants in Burundi [^10^](#_ENREF_10). Based on the prevalence of malnutrition (<-2sd in any of HAZ,WAZ,BMIZ) among the CURIE CP population based cohort reported as 64% as per the 2015 assessments. Assuming the previously reported effect of the PD program, we hope to reduce malnutrition in the CP child population to about 29%, at α =0.05, and power (1-β) =0.8. After imputing these parameters into a Stata program to estimate sample size for individual randomization, of a two proportions test, the estimated total sample size is 62: Hence 31 participants per each of the four arms. Therefore for a 2x2 factorial trial, assuming a 1:1:1:1 allocation, 124 participants will be required for the study with 32 participants in each of the four conditions.

Participants in this study will include eligible caregivers of children with CP participating in the wider CURIE intervention study (Akwenda). In order to account for those that may not be malnourished from the CURIE study sample, additional caregivers of malnourished children with CP will be recruited from community-based organizations (CBOs) operating within the study setting including EKISA ministries and MUSANA community health centre. The CURIE intervention study has got two arms (PFT and Control) separated as village clusters based on geographical proximity and balanced by age, and GMFCS level. This study will utilize the available CURIE intervention clusters to avoid contamination. Details of participant recruitment from different CBOs are displayed below.

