**Data management and analysis.**

Descriptive statistics will be performed by tabulation of the summary means of the individual condition levels and baseline social demographic characteristics of the children and their caregivers. Participants’ characteristics will be presented in frequency tables. A two-way analysis of variance (ANOVA) will be performed to test the independent main effects of PD and PFT, and the effect of interaction of both PD and PFT. Factor levels will be compared by a pairwise comparison of treatment means (standard error of a difference) or a fisher’s least significant difference (LSD) test. This analysis will be done in both intention to-treat and per-protocol assumptions. All analysis will be expressed in 95% two sided confidence intervals and a p-value of <0.05 will indicate statistical significance.

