**Severe (exclusion)**

MUAC <11.5cm (Child),

<-3SD with Oedema

**Malnourished (inclusion)** N=124

<-2SD WHZ, HAZ, WAZ, MUAC

CURIE-No PFT control cluster

CURIE-PFT intervention cluster

-Caregiver counselling on immediate management of severe malnutrition

-Referral for management

Allocation and randomization

Follow-up

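### The stated 80% power uses a 64% comparison rate taken from the whole CP cohort, but the trial enrols only malnourished children, so that power does not describe the enrolled sample

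*Protocol*

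**What the plan says.** The Protocol's section on sample size estimation has two calculations.

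- The first is a precision calculation for a main effect in a 2x2 factorial: within-group error variance 8.0, confidence interval width 2.0, 95% confidence, contrast coefficients ±0.5. It gives about 31 per group.
- The second compares two proportions. Its starting rate is "Based on the prevalence of malnutrition (<-2sd in any of HAZ,WAZ,BMIZ) among the CURIE CP population based cohort reported as 64" per cent, from the 2015 assessments. The target follows: "we hope to reduce malnutrition in the CP child population to about 29" per cent, "at α =0.05, and power (1-β) =0.8". The result is "the estimated total sample size is 62: Hence 31 participants per each of the four arms", and then "assuming a 1:1:1:1 allocation, 124 participants will be required for the study".

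The study population section restricts entry: "The study population will include caregivers of malnourished children and youth aged 2-24 years old with a confirmed diagnosis of CP". The section defining malnutrition uses a Z-score below -2 SD in any indicator, the same cut-off that lies behind the 64%, and ties enrolment to moderate acute malnutrition. The flow chart labels the entry box "Malnourished (inclusion)" with N=124. The sample size section itself says that cohort members who turn out not to be malnourished will be made up for by malnourished children from community-based organisations.

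**The concern.** The 64% is a cross-sectional share among all children with CP in the cohort. It is below 100% only because 36% of that cohort were not malnourished, and the trial does not enrol such children. In the enrolled sample the share malnourished at entry is therefore close to 100%. It may fall slightly short if some children enter on mid-upper arm circumference alone, but that does not lead back to 64%.

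To serve as the comparison rate in a trial of this sample, 64% would have to be the share of children without PD who are still malnourished at follow-up. About 36% of them would then have to rise above -2 SD on all three indicators, height-for-age included, within the 3-month trial. The protocol does not state or justify such an assumption; it describes 64% only as a prevalence.

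At stake is the protocol's only power statement. The precision calculation gives an interval width, not a power, so the 80% rests entirely on the 64% v 29% contrast.

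**Working it through.** **Inputs from the Protocol.** p1 = 0.64, p2 = 0.29, α = 0.05, power 0.80, 31 per condition and 62 per factorial margin (sample size section and Table 1). The test is taken as two-sided because the analysis section says "All analysis will be expressed in 95% two sided confidence intervals".

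**Step 1: reproduce the plan's figure.** Pooled formula without continuity correction, n per group:

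n = [1.96·√(2·p̄(1−p̄)) + 0.8416·√(p1(1−p1) + p2(1−p2))]² / (p1−p2)²

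With p̄ = (0.64 + 0.29)/2 = 0.465, the two roots are 0.7054 and 0.6605:

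n = (1.96 × 0.7054 + 0.8416 × 0.6605)² / 0.35² = 30.7, so 31 per group and 62 in total.

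Power at 31 v 31 is 80.4%. The stated figure is reproduced; the fault lies in the input, not the arithmetic.

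**Step 2: check whether the total depends on this input.** In the precision calculation the squared contrast coefficients sum to 4 × 0.25 = 1, so

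n = 4 × 8.0 × 1 × (1.96/2.0)² = 30.7, about 31 per group.

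Neither 64% nor 29% enters. The total of 124 therefore has a second support.

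**Step 3: what 64% would mean at follow-up.** Entry about 100% malnourished, follow-up 64%, so 100 − 64 = 36% recovered without PD. The protocol gives no such figure.

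**Step 4: power with a control rate suited to an all-malnourished sample.** The documents give no such rate. I assume that 85%, 90% or 95% of children without PD are still malnourished at 3 months. Using the same pooled formula, with n per compared group,

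power = Φ{[(p1−p2)·√n − 1.96·√(2·p̄(1−p̄))] / √(p1(1−p1) + p2(1−p2))}

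The protocol's planned effect can be read as an absolute drop (64 − 29 = 35 points) or as a ratio (29/64 = 0.453). The 20-point drop is my own illustration of a smaller effect.

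| Effect | Control v PD | Power at 31 v 31 | Power at 62 v 62 |
| --- | --- | --- | --- |
| 35-point drop | 85 v 50% | 86% | 99% |
| | 90 v 55% | 89% | >99% |
| | 95 v 60% | 93% | >99% |
| Ratio 29/64 | 85 v 38.5% | 98% | >99% |
| | 90 v 40.8% | 99% | >99% |
| | 95 v 43.0% | >99% | >99% |
| 20-point drop | 85 v 65% | 44% | 74% |
| | 90 v 70% | 50% | 80% |
| | 95 v 75% | 60% | 89% |

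The 62 v 62 column is the main-effect comparison of PD against no PD, pooled over the two parent facilitator training levels. It treats children as independent and makes no allowance for dropout.

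**The case against.** The strongest reply is that the mismatch changes little. The precision calculation reaches the same 31 per group without the 64%. On either reading of the protocol's own planned effect, a higher control rate raises power. The factorial tests main effects at 62 v 62, where even a 20-point drop has 74–89%. Malnutrition status is also not the primary outcome, which is weight gain. All of this stands, and it limits the point to the power statement. It does not make 64% a valid control rate.

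Four stronger readings are tempting, and the documents do not support them.

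- *That the trial is underpowered.* Power falls below 80% only if a smaller effect than the protocol's is assumed as well. The higher control rate alone moves power upwards.
- *That the N of 124 falls with this input.* It does not, because of the precision calculation.
- *That a 64% control rate is impossible.* It is arithmetically possible at follow-up, but it is unstated and unsupported.
- *That 64% can serve as a screening yield, giving 124/0.64, or about 194, to screen.* The 64% counts everyone below -2 SD, including severe cases that the trial excludes and refers. The protocol also excludes caregivers registered in other nutrition interventions, and it takes some children from community-based organisations rather than from the cohort.

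**Conclusion.** Wrong as written, confined to the power statement. The protocol takes a whole-cohort prevalence as the comparison rate for a sample selected to be malnourished, so the stated 80% does not describe the trial being run. The calculation itself is correct, and N=124 does not depend on it alone.

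The size and direction of the error cannot be fixed from the document. With an assumed control rate of 85–95%, power at 31 v 31 is 86–93% for a 35-point drop, 98% or more for the planned ratio, and 44–60% for a 20-point drop. At 62 v 62 the corresponding figures are 99% or more, above 99%, and 74–89%. These rest on my assumed control rates, the pooled two-sided test at 0.05, independent children and complete follow-up.

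**What to change.** In the sample size section, stop using the cohort prevalence as the control rate. Keep N at 124. State explicitly, as an assumption with its source, the outcome rate expected without PD among enrolled malnourished children, and give the resulting power at the 62 v 62 main-effect margin over a range of PD effects. Preferably do this for the primary outcome in the outcome measures section (weight gain), since power for persisting malnutrition would not carry over to it. The 64% may stay as background on the cohort, but no number to screen should be derived from it.

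The cost is some wording and one recalculation. The restated power may be less favourable than 80% if a modest PD effect is considered realistic.
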